#### PLAYgrounds for Toddlers

The initial ‘PLAYgrounds’ program concerns a physical education based playground program for primary schools to improve physical activity levels of children during recess times. The program consists of a multi-component alteration of the schools’ playground. In addition, the playground usage is stimulated by altered time management of recess times, teachers stimulating physical activity and a modification of the physical education content. ‘PLAYgrounds’ is proven to be effective in primary schools [17, 18]. For PS@HW, the program was adapted to the context and target group on preschools of child care organization Impuls. This ‘PLAYgrounds’ program for toddlers focusses on the amount and type of physical activity and the prompts of ECEC teachers within the possibilities of the outdoor space and availability of material in preschools. Two training sessions and 1 evaluation session will be organized for in total 4 groups of ECEC teachers. In addition, a trainer will visit each preschool in the intervention group between the training sessions to give specific instructions for improvement (coaching on the job) to the local team of ECEC teachers.

In PS@HW, ‘A Healthy Start’ and ‘PLAYgrounds for Toddlers’ have a complementary role. The multi-component and multilevel programs share a focus on providing a healthy and active environment for toddlers and the role of ECEC teachers to set a healthy example. The interventions will be applied consecutively, in order not to overload ECEC teachers. Attendance records will be used to determine the adherence of ECEC teachers to the intervention. All participants who will attend at least 2 meeting of ‘A Healthy Start’ and 1 meeting of ‘PLAYgrounds for Toddlers’ will receive certificates.

### Procedures and outcome measures

ECEC teachers and parents will be asked to fill in a questionnaire at baseline, 4 months follow-up (only applicable for ECEC teachers) and 9 months follow-up (close-out). At the same time, anthropometric measurements in ECEC teachers and toddlers will be carried out. Furthermore, observations on the playgrounds will be performed at 4 and 9 months follow-up. The questionnaire for ECEC teachers includes questions on knowledge, attitude and practices regarding healthy eating and physical activity, and questions on the level of confidence in promoting healthy eating and physical activity in toddlers. For parents, the questionnaire includes questions on knowledge, attitude and practices regarding healthy eating and physical activity of their toddler. In addition, ECEC teachers and parents will be asked to fill in a 3-day food and physical activity record at baseline and 9 months follow-up (parents fill in the records for their toddler).

All measurements will be carried out by trained research staff and students of the Amsterdam University of Applied Sciences using Standard Operation Procedures. The study team is coordinated by 3 unblinded researchers ([name]) and 1 blinded researcher (MS).

Questionnaires, score forms and records will be coded to protect the privacy of the participants. Data from paper questionnaires and score forms will be handled into Microsoft Excel by double data-entry. Records will be entered in Microsoft Excel and checked by trained research staff and students of the Amsterdam University of Applied Sciences.

Table 1 provides a summary of the outcome measures for the study timepoints.

**Table 1 Tab1:** Summary of the outcome measures for the study timepoints

TIMEPOINT	BASELINE			4 MONTHS					9 MONTHS		
	ECEC*	Toddlers	Parents		ECEC*	Toddlers	Parents		ECEC*	Toddlers	Parents
OUTCOME MEASURES											
*Demographic data*	X	X	X								
*Knowledge of Dutch food-based dietary guidelines*	X		X		X				X		X
*Attitude about healthy eating and physical activity*	X		X		X				X		X
*Food and activity practices*	X		X		X				X		X
*Level of confidence in promoting healthy eating and physical activity*	X				X				X		
*Anthropometry and body composition*	X	X			X				X	X	
*Dietary intake*	X	X							X	X	
*Physical activity level*	X	X							X	X	
*Role (prompts) on playground*					X				X		
*Amount and type of physical activity on playground*						X				X	
*Motor development*		X								X	
*Weight perception of weight status toddler*			X								X

**ECEC* Early Childhood Education and Care teachers

#### Demographic data

The questionnaire for ECEC teachers and parents includes demographic questions to obtain general characteristics of the study population. Data of ECEC teachers, toddlers and parents will be collected, including the date of birth (age will be calculated in years (adults) and months (toddlers)), gender, country of birth (migration background) and level of education (proxy for socio-economic status, only applicable for ECEC teachers and parents).

#### Knowledge, attitude and practices regarding healthy eating and physical activity

The knowledge of ECEC teachers and parents will be assessed by 2 types of questions. Firstly, subjects will be asked to answer 10 statements on the Dutch food-based dietary guidelines with ‘True’, ‘False’ or ‘Don’t know’ [19]. Secondly, subjects will indicate in 3 separate questions if 5 food products (in total 15 food products) are ‘High’ or ‘Low’ in respectively added sugars, salt and fibres (or if they ‘Don’t know’) [20]. A sum score for Knowledge will be calculated; each correctly answered question yields one point with a maximum of 25 points.

Attitudes will be evaluated through individual statements regarding healthy eating and physical activity. The statements are compiled by the research staff. For example, ECEC teachers and parents will be asked to answer to what extent they do agree with the following statement: ‘I feel responsible for healthy nutrition- and physical activity patterns of my/the child(ren). A 5 point Likert-scale will be used. Answering options for the statements are 1) totally disagree (1 point), slightly disagree (2 points), neutral (3 points), slightly agree (4 points) or totally agree (5 points).

A modified version of the Child-care Food and Activity Practices Questionnaire (CFAPQ) [21] will be used to assess the practices of ECEC teachers related to food and physical activity. The original CFAPQ consists of 63 items (40 food-related and 23 activity-related items), divided over 12 CFAPQ scales (7 food-related and 5 activity-related scales). For the original CFAPQ, Gubbels et al. show a sufficient internal consistency in the CFAPQ scales with a Cronbach’s α ranging from 0.53 to 0.96 [21]. In PS@HW, a modified version of the CFAPQ will be used as not all CFAPQ scales are applicable for preschools. The PS@HW questionnaire for ECEC teachers includes the following 7 CFAPQ scales: Food-related Modelling/Encourage balance and variety, Food-related Teaching about nutrition, Food-related pressure to eat, Activity-related modelling, Activity-related psychological control, Activity-related teaching/autonomy support, Activity-related going outdoors and 1 single item about the availability of outdoor toys. Answering options for the questions are 1) totally disagree (1 point), slightly disagree (2 points), neutral (3 points), slightly agree (4 points), totally agree (5 points) or 2) never (1 point), rarely (2 points), sometimes (3 points), mostly (4 point), always (5 points). A mean score per CFAPQ scale will be calculated.

For parents, the Comprehensive Feeding Practices Questionnaire (CFPQ) [22] and the Preschooler Physical Activity Parenting Practices (PPAPP) instrument [23] will be used to assess parenting practices. The parenting practices questionnaires are both starting points for the CFAPQ (selected items of the questionnaires are converted to the child care setting by Gubbels et al.). The original CFPQ includes 12 CFPQ scales on food related practices. One CFPQ scale about restriction for weight control is considered to be too extensive for the purposes of PS@HW. Consequently, the following 11 CFPQ scales are incorporated in the PS@HW questionnaire for parents: Child control, Emotion regulation, Encourage balance and variety, Environment, Food as reward, Involvement, Modeling, Monitoring, Pressure, Restriction for health and Teaching about nutrition. The PPAPP concerns questions about encouraging and discouraging practices related to physical activity of children. The encouraging practices consist of 1 PPAPP scale (Engagement) and 2 single items (Not register the child for sports or dance due to lack of money and Having outdoor toys available for the child). The discouraging practices consist of 4 PPAPP scales, namely Promote inactivity, Promote screen time, Psychological control and Restriction for safety. The complete PPAPP is incorporated in the PS@HW questionnaire for parents. Answering options for the questions are 1) totally disagree (1 point), slightly disagree (2 points), neutral (3 points), slightly agree (4 points), totally agree (5 points) or 2) never (1 point), rarely (2 points), sometimes (3 points), mostly (4 point), always (5 points). A mean score per CFPQ and PPAPP scale will be calculated.

#### Level of confidence

The level of confidence of ECEC teachers related to promoting healthy eating and physical activity in toddlers, will be assessed using a confidence ruler [24]. ECEC teachers indicate, on a scale of 1 (not confident at all) to 10 (extremely confident), how confident they are in supporting toddlers (and their parents) in healthy eating and physical activity.

#### Anthropometry and body composition

In ECEC teachers and toddlers, body weight (kg) will be measured using a portable weighing scale (Seca 813) without shoes or heavy clothing. Moreover, body height (cm) will be measured with a portable stadiometer (Seca 213) without shoes. BMI (kg/m^2^) will be calculated. For toddlers, also the BMI z-score will be assessed using World Health Organization reference data (WHO Anthro). Weight status of the toddlers (underweight, normal weight, overweight and obesity) will be evaluated by reference data of Cole et al. [25]. In addition, the weight perception of parents concerning the weight status of their toddler will be examined via a question in the questionnaire for parents (answering options are: underweight, normal weight, overweight, severe overweight).

Total body resistance will be measured in ECEC teachers and toddlers by Bioelectrical Impedance Analysis (Bodystat 1500 MDD). The measured resistance will be used to calculate Total Body Water and subsequently Fat Free Mass and Fat Mass (kg/%) [26, 27]. For toddlers, hydration constants discussed by Fomon et al. will be used in the calculation of Fat Free Mass [28]. Furthermore, the Fat Mass Index (kg/m^2^) will be evaluated for toddlers.

#### Dietary intake

The dietary intake of ECEC teachers and toddlers will be estimated by 3-day food records. Food records are described to be useful in the estimation of dietary intakes in culturally diverse populations [29]. ECEC teachers will be asked to record their dietary intake per meal on 2 working days and 1 weekend day. Parents will be asked to fill in the 3-day food record for their toddler on 2 week days and 1 weekend day. Written and oral instructions will be given by the research staff. The intake of foods will be converted (by coding and converting household measures into grams) into energy and nutrient intake using the Dutch Food Composition Database 2016 [30] and a database with portion sizes [31].

#### Physical activity level

The physical activity level of ECEC teachers and toddlers will be determined using 3-day physical activity records. Self-report measures are commonly used to estimate physical activity levels [32] and are considered to be feasible for the purposes of PS@HW. ECEC teachers will be asked to record activities per 0.5 h on 2 working days and 1 weekend day. Parents will be asked to fill in activities for their toddler per 0.5 h during 2 week days and 1 weekend day. MET-scores will be assigned to each activity in order to calculate physical activity levels. For ECEC teachers, the 2011 Compendium of Physical Activities will be used as a reference for MET-scores [33]. For toddlers, a Youth Compendium of Physical Activities described by Butte et al. will be used [34]. In addition, ECEC teachers will be asked to wear an accelerometer (ActiGraph ActiTrainer) for 6 days to obtain objective data on their physical activity level. The data obtained by the ActiTrainers will be processed in the ActiLife Data Analysis Software version 5.10.0. Counts per minute will be assessed and the intensity of physical activity will be evaluated (sedentary to very vigorous).

#### The activating role of ECEC teachers and amount & type of physical activity in toddlers on the playground

To investigate the activating role of ECEC teachers regarding physical activity of toddlers on the playground, it was chosen to perform systematic observations on the playground of preschools. Furthermore, the amount and type of physical activity in toddlers on the playground will be systematically observed. As part of the ‘PLAYgrounds for Toddlers’ program, trained research assistants will perform the observations based on the SOPLAY protocol (physical activity levels during play time) [35]. This standardized protocol includes observations on the amount of physical activity, type of physical activity and aspects related to the physical environment (for example, weather conditions and provision of playground equipment). Before and after the ‘PLAYgrounds for Toddlers’ program, 2 observations on each playground will be performed.

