## Methods

### Study design and setting

PS@HW concerns a cluster randomized controlled trial. Preschools of child care organization Impuls in Amsterdam Nieuw-West, the Netherlands, were randomly allocated to an intervention or control group by an independent researcher (with the use of computer-generated randomization lists). The study period is 9 months, starting with baseline measurements and ending with close-out measurements. For ECEC teachers, additional data will be collected after 4 months of follow-up. After the baseline measurements, a preschool-based intervention regarding healthy eating and physical activity will be carried out on preschools in the intervention group. The intervention consists of modified versions of 2 existing Dutch programs for ECEC teachers: ‘A Healthy Start’ (Dutch: Een Gezonde Start) and ‘PLAYgrounds’. Figure 1 provides a schematic overview of the study.

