### Recruitment

In total, 42 preschools of child care organization Impuls were available for allocation. One location was excluded because of practical reasons and 4 preschools were combined in the allocation as they shared a building or playground. The final sample includes 41 preschools, in which 115 ECEC teachers and 249 toddlers and their parents were recruited. ECEC teachers who worked at multiple preschool locations were excluded. Toddlers and their parents were included if the toddler was 2.5 to 3.5 years old. ECEC teachers and parents received oral and written information about the study. For ECEC teachers, information meetings were organized. Parents were individually approached by the research staff. All participating ECEC teachers and parents gave written informed consent. Parents gave additional written informed consent for their toddlers.

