### Planned statistical analysis

The sample size is based on a medium effect size (Cohen’s d: 0.50), a 1-sided alpha of 5% and a power of 80%, taken into account a design effect (mean cluster size = 3, ICC: 0.05) and a 10% drop-out rate.

Descriptive statistics (percentages, mean ± SD, or median (IQR)) will be used to describe the characteristic of the study population.

Mixed Model analyses will be used for the effect evaluation with primary and secondary outcome measures at the level of ECEC teachers, toddlers and their parents. Time, treatment (intervention or control group) and their interaction are fixed factors. Subject and location will be included as random factors to take into account the clustered data structure.

For the purpose of implementing the preschool-based intervention on organizational level, a process evaluation focusing on the acceptance, satisfaction and improvements of the intervention will be performed.

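### Playground outcomes rest on few outdoor observations, and weather is recorded but absent from the stated model, so precision is lost; one visit calendar for both arms is also not fixed

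*Protocol article*

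**What the plan says.** Protocol article, Procedures and outcome measures: "observations on the playgrounds will be performed at 4 and 9 months follow-up". Table 1 agrees: the playground rows are marked at 4 and 9 months and not at baseline.

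Protocol article, The activating role of ECEC teachers and amount & type of physical activity in toddlers on the playground: the observations follow a SOPLAY-based protocol that covers the amount and type of activity and "aspects related to the physical environment (for example, weather conditions and provision of playground equipment". The timing is given relative to the PLAYgrounds for Toddlers program, on either side of it: "2 observations on each playground will be performed".

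Protocol article, Planned statistical analysis: one mixed model is given for every outcome, whether primary or secondary and whether measured in teachers, toddlers or parents. Its fixed part reads: "Time, treatment (intervention or control group) and their interaction are fixed factors". Its random part consists of an effect for the person and one for the preschool. No weather or season term is listed, and no separate model is given for the playground outcomes.

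Protocol article, Study design and setting: the preschools "were randomly allocated to an intervention or control group by an independent researcher". The intervention, including the playground program, is delivered at intervention preschools only.

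**The concern.** Activity in an outdoor space is likely to depend on the weather during the visit. With so few visits per playground, one wet or cold day carries much weight. The random location effect absorbs stable differences between playgrounds, such as size or layout, but not the conditions on a given day. Those go into the residual error, although the information to remove part of them is already collected.

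A second question is timing. One section gives 4 and 9 months for everyone. The other anchors the visits to a program that control preschools do not receive. It is run for four groups of teachers, with coaching visits between sessions. For control playgrounds that second anchor has no meaning, and no rule links the two. If the arms were in fact visited in different weeks, a weather or calendar difference would be read as a program effect.

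These outcomes are secondary. They are, however, the only directly observed measure of toddlers' activity at preschool and of the teachers' activating role: the toddlers' other activity measure is a parent-completed record, and the accelerometer is for teachers only.

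**Working it through.** **No stated figure to reproduce.** The sample size paragraph (effect size 0.50, one-sided 5%, 80% power, cluster size 3, ICC 0.05, 10% drop-out) gives no variance, power or number for the playground outcomes.

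**Inputs from the article.** Two rounds, at 4 and 9 months; 2 observations per playground, per round or in total; 41 preschools. The Recruitment section adds: "One location was excluded because of practical reasons and 4 preschools were combined in the allocation as they shared a building or playground". That may leave about 38 to 40 allocation units, depending on how they were combined.

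**Assumptions.** Allocation about 1:1 (20 and 21 preschools); non-weather observation SD set to 1; weather SD *w* of 0.5 or 1.0 on that scale; weather drawn independently for each visit.

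**1. Does a season shift between rounds enter the effect?** The treatment effect is the difference between arms in the 4-to-9-month change. A shift *s* shared by both arms gives (change₁ + s) − (change₀ + s) = change₁ − change₀, so *s* drops out. Simulation (20,000 runs per setting, true effect 0, 41 clusters, 2 observations per round, shared season shift of 0 or 1 SD, *w* = 0, 0.5 or 1.0) gave mean bias within 0.01 SD and two-sided type I error of 4.9–5.2%.

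**2. What does unadjusted weather cost?** With *m* observations per round,

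SE = √[ 2(1 + w²)/m × (1/20 + 1/21) ], where 1/20 + 1/21 = 0.0976.

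| w | m = 2 | m = 1 | Relative to w = 0, √(1 + w²) |
|---|---|---|---|
| 0 | √(1.00 × 0.0976) = 0.31 | √(2.0 × 0.0976) = 0.44 | 1.00 |
| 0.5 | √(1.25 × 0.0976) = 0.35 | √(2.5 × 0.0976) = 0.49 | 1.12 |
| 1.0 | √(2.00 × 0.0976) = 0.44 | √(4.0 × 0.0976) = 0.62 | 1.41 |

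The simulated standard errors agree to within 0.01. The column m = 1 is the reading of two observations in total.

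**3. What would adjustment recover?** If the covariate explains a share R² of the observation-level variance, the SE falls by 1 − √(1 − R²), which is worth 1/(1 − R²) − 1 more observations.

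- R² = 0.10: 1 − √0.90 = 5%; 1/0.90 − 1 = 11%.
- R² = 0.30: 1 − √0.70 = 16%; 1/0.70 − 1 = 43%.

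This range corresponds to a weather SD of √(0.10/0.90) = 0.33 to √(0.30/0.70) = 0.65. At *w* = 1.0, R² would be 1/(1 + 1) = 0.50 and the most that could be recovered 1 − √0.50 = 29%.

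**4. How often are the arms unbalanced by chance?** Take 20 playgrounds per arm, with each playground's pair of visits sharing its weather, and 30% or 50% poor-weather visits (assumptions). Under exact binomial counts, the shares differ by more than 20 points with probability 12% (at 30%) to 15% (at 50%) per round. With all 40 observations per arm independent, the figures are 4% and 6%. A normal approximation without continuity correction gives 17–21% and 5–7%, which is too high at these counts. If poor weather lowers activity by 0.5–1.0 SD (assumption), a 20-point imbalance moves that round's arm difference by 0.20 × 0.5 = 0.10 to 0.20 × 1.0 = 0.20 SD. This is random error and part of the standard error in step 2.

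**5. What if the arms were visited at different times?** An arm-specific shift of 0.25, 0.5 or 1.0 SD in one round (41 clusters, m = 2, *w* = 0.5) passed into the estimate in full, with two-sided type I error of 10%, 29% and 80%. These are consequences of an assumed misalignment; the article does not report one.

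**The case against.** **Covariates belong in the analysis plan.** The Planned statistical analysis section is a short summary for all outcomes. It does not say that weather will be ignored, and an outcome-specific covariate may sit in a plan that is not shown. This stands in part: the article contains no error here. But the model it prints is explicit, is said to cover the secondary outcomes and has no such term, so the suggestion improves on a stated method.

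**The schedule may already be common to both arms.** Procedures and outcome measures and Table 1 give the same two time points without distinguishing arms, and the wording around the program may simply describe those two rounds. Visit calendars may also be in the Standard Operation Procedures, which are not shown. This stands against any claim that the arms are visited at different times. It does not remove the ambiguity for control playgrounds.

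**Stronger readings do not hold.** A reader might infer that the five-month gap puts season into the treatment effect. It does not, because the arms are randomised and concurrent and a shared shift cancels (step 1). A reader might also take a chance imbalance in weather as bias. It is noise that the standard error already carries.

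**The sizes are assumed.** This stands. The article gives no weather frequency, weather effect or explained variance.

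**Conclusion.** The point holds as one of precision on secondary outcomes. Few outdoor observations per playground are analysed with a stated model that makes no use of the weather recorded at them. If weather explains 10–30% of the observation-level variance, adjustment reduces the standard error by about 5–16%. That range is an assumption, and the gain depends on how well the recorded categories capture the weather effect.

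The documents do not support a finding of bias. Season enters the effect only if the arms are visited in different weeks. The article does not state this, but does not exclude it, because its two timing statements are not tied together for control playgrounds. Chance imbalance of more than 20 points in poor-weather visits, in about 12–15% of rounds under the assumptions in step 4, is random error. The conclusion that the standard error covers it rests on visits having independent weather; playgrounds of one arm clustered on the same days would weaken it, which is a further reason to fix the calendar.

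The change is worth making because it is nearly free. No stated figure is wrong.

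**What to change.** 1. In the model for the playground outcomes, add the recorded weather (for example dry or wet, and temperature if it is noted) as a prespecified observation-level covariate. Do not adjust for provision of playground equipment: the program may change it, and adjustment could remove part of the effect.
2. State one calendar rule for both arms, so that intervention and control playgrounds are visited in the same weeks of each round, and reconcile the two timing statements for control sites. Where visits have already taken place, tabulate visit dates and weather by arm and round.
3. Say whether the 2 observations are per round or in total.

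Cost: one or two model degrees of freedom and slightly less scheduling freedom. No new data collection is needed.
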